**Demographic and socioeconomic data, lifestyle factors**				
Age, sex, place of birth, marital status, nationality, employment status, occupation, level of education, smoking status (past, current, never), and alcohol consumption (none, occasional, moderate, and heavy consumption), dietary habits, physical activity, sleep quality, and vacation frequency	+			
**Medical data**				
Timing and characteristics of prior TIA or stroke	+			
Vascular risk factors (hypertension, diabetes mellitus, dyslipidemia, atrial fibrillation	+			
Comorbid conditions (including genetic disorders), history of seizures	+			
Past and current medication use	+	+	+	+
Body mass index (BMI)	+			
**Neurological and cognitive**				
Baseline neurological examination findings	+			
Modified Rankin Scale (mRS)	+	+	+	+
National Institutes of Health Stroke Scale (NIHSS) scores	+	+	+	
Quality-of-life measures (questionnaire)	+	+	+	
Cognitive reserve indicators (educational attainment and occupational complexity), and engagement in cognitively stimulating activities	+			
**Imaging examinations**				
CTA	+	+	+	+
DSA	+			
MRI ASL	+	+	+	
**Hemodynamic parameters**				
Collateral circulation patterns	+			
Location and length of the internal carotid artery occlusion	+			
Circle of Willis configuration	+			
ASL perfusion metrics	+	+	+	
Cerebral blood flow (CBF) asymmetrical indices	+	+	+	
Infarct burden	+	+	+	
White matter hyperintensities	+			
Bypass patency and the diameter of STA		+	+	+

Abbreviations: Preop – preoperatively, PostOp0 – Immediately postoperatively, PostOp6–6 months postoperatively, UV – Unscheduled Visit, TIA – transient ischemic attack, BMI – Body mass index.

Included patients will undergo CTA of the head and neck vessels with a slice thickness of 0.5-0.625 mm to confirm ICA occlusion and to measure the diameter of the donor STA branch at 2 mm distal to its bifurcation.

MRI perfusion studies will be conducted before surgery on 1.5 or 3 Tesla MRI to evaluate cerebral blood flow (CBF) and determine the extent of cerebrovascular insufficiency. The main perfusion method will be ASL, which will provide quantitative CBF values, assess the degree of perfusion deficit, and reveal signs of compensatory collateral circulation based on the presence of arterial transit artifacts (ATA). Imaging parameters are described in in S1 Table.

DSA will be performed using a biplane digital subtraction angiography system (Artis Zee, Siemens) with a 6F guiding catheter at a frame rate of 7.5 frames per second. The angiographic assessment will evaluate the presence of communicating arteries, the completeness of the Circle of Willis, and the extent of collateral circulation. Hemodynamic compensation will be quantified by analyzing filling times and phase delays across the arterial, parenchymal, and venous phases, expressed in frames. Image analysis will be conducted using Siemens Artis Q angiography software to ensure accurate and reproducible measurements.

#### Neurological assessment.

The degree of neurological deficit before and after surgery will be evaluated by neurologist using the Baseline neurological examination findings, mRS and National Institutes of Health Stroke Scale (NIHSS) scores. The consequences of prior stroke will also be assessed with the mRS [15] and the Functional Activities Questionnaire (FAQ) [17]. Preoperatively and six months after surgery, all patients will be evaluated under a unified diagnostic protocol, with results collected and recorded separately before entering them into a general database with strict personal data encoding.

#### Cognitive function assessment.

Changes in cognitive function before and after surgery and six months postoperatively will be assessed using the neuropsychological tests, measuring both verbal and non-verbal IQ.

A standardized battery of neuropsychological tests will be administered by a psychologist to evaluate global cognition, memory, visuospatial skills, and executive function (S2 Table). The Montreal Cognitive Assessment (MoCA) will be used as a screening tool for global cognitive function, assessing domains including attention, executive functions, memory, language, visuospatial skills, abstraction, and orientation [18]. The Rey Auditory Verbal Learning Test (RAVLT) will be employed to evaluate verbal learning and memory performance, including immediate recall, delayed recall, and recognition memory [19]. Nonverbal test of Kohs Block Design will be used to assess visuospatial reasoning, problem-solving, and perceptual-motor coordination by requiring participants to reproduce geometric patterns with colored blocks [20]. The Stroop Test will be applied to measure selective attention, processing speed, and cognitive flexibility by evaluating the ability to inhibit cognitive interference [21].

To minimize potential learning or practice effects associated with repeated testing, assessments will be conducted at predefined intervals with sufficient time between evaluations, and standardized administration procedures will be maintained across all sessions. Whenever available, alternative test versions will be used for repeated assessments.

Neuropsychological test performance will be interpreted using age- and education-adjusted normative data when available, in order to reduce the potential confounding effect of educational background on cognitive outcomes.

#### Perioperative management.

Perioperative management was standardized for all patients to minimize treatment variability and potential confounding effects on outcomes. General anesthesia was performed using a standardized protocol with continuous hemodynamic monitoring. Intraoperative blood pressure was strictly controlled to avoid hypotension or excessive fluctuations that could compromise cerebral perfusion or graft flow. Postoperatively, patients were monitored in a dedicated intensive care unit with close neurological interventional and continuous blood pressure control. Systolic blood pressure targets were maintained within a predefined range to ensure adequate bypass perfusion while minimizing the risk of hyperperfusion-related complications.

All patients received standardized antiplatelet therapy with aspirin 100 mg once daily, initiated preoperatively or immediately postoperatively according to the institutional protocol, and continued throughout the follow-up period unless contraindications developed.

#### Surgical treatment.

Eligible patients with chronic ICA occlusion will undergo standard STA-MCA bypass surgery. The procedure will be carried out using a standardized microsurgical end-to-side anastomosis technique. Intraoperative selection of the donor STA branch and recipient MCA segment will be based on vessel diameter, flow characteristics, and surgical accessibility. Intraoperative bypass patency will be assessed using the “faucet” technique” [22] in combination with microscopic indocyanine green (ICG) angiography to ensure adequate flow through the anastomosis.

#### Intraoperative perfusion and blood flow direction assessment.

Intraoperative perfusion and blood flow direction will be assessed using ICG fluorescent angiography with the Carl Zeiss Pentero 800 microscope equipped with FLOW 800 technology, which allows real-time visualization of cerebral vessels. All data will be processed and analyzed to create a color map depicting hemodynamic and perfusion delays. This enables comparison of perfusion parameters in the anastomosis region before and after bypass surgery, as well as assessment of blood flow direction and hyperperfusion zones in the brain. The assessment will be performed by neurosurgeons.

#### Postoperative study procedures.

Within 1-3 days after surgery, CTA of the head and neck will be performed to confirm bypass patency, measure the caliber of the donor STA branch, and visualize its course. At 3–5 days postoperatively, ASL-based MR perfusion imaging will be conducted to evaluate cerebral perfusion changes compared with preoperative studies. 3D segmentation and quantitative perfusion mapping will be applied to provide an objective assessment of regional perfusion improvements following surgery. Before hospital discharge, all patients will undergo a repeat evaluation of neurological status and cognitive function using the same standardised tests as preoperatively.

#### Follow-up assessment.

At six months after surgery, all patients will undergo follow-up assessment including CTA of the head and neck to evaluate bypass patency and measure the caliber of the donor STA branch, MR perfusion imaging with 3D segmentation to assess cerebral perfusion changes, and repeat neurological and neuropsychological evaluations using the same tests administered preoperatively and at discharge (NIHSS, mRS, MoCA, RAVLT, Kohs Block Design, and Stroop tests). The planning of the follow-up is described in Table 1.

### Study endpoints

#### Primary endpoint.

To evaluate the incidence of ischemic stroke during the 6-month follow-up period after surgery.

#### Secondary endpoints.

Early postoperative graft patency, perioperative safety, neurological and cognitive outcomes, recurrent cerebrovascular events, mortality, and radiological markers of revascularisation.

#### Definitions of outcomes.

The primary outcome is defined as the incidence of ischemic stroke during the 6-month follow-up period after surgery. This outcome will be assessed based on clinical evaluation and confirmed by neuroimaging (MRI or CT) in cases of suspected new neurological deficits, in accordance with standard diagnostic criteria for ischemic stroke.

Secondary outcomes included early postoperative haemodynamic change (≤7 days) assessed using the same imaging modality; graft patency was defined as uninterrupted flow through the bypass on intraoperative ICG and postoperative CTA; changes in cerebral haemodynamic status from baseline to 6 months after surgery will be assessed using ASL MRI and defined as a quantitative increase in regional CBF in the affected hemisphere and/or a reduction in interhemispheric perfusion asymmetry compared with baseline; change in neurological status from baseline to 6 months assessed using the NIHSS and the mRS; changes in cognitive function from baseline to 6 months based on standardised neuropsychological testing; all-cause mortality at 6 months; perioperative complications within 30 days (including intracranial haemorrhage, hyperperfusion syndrome, seizures, wound complications, and graft occlusion); and angiographic extent of revascularisation on follow-up imaging.

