### Eligibility criteria

#### Inclusion.

Chronic ICA occlusion confirmed by computed tomography angiography (CTA), magnetic resonance angiography (MRA), and digital subtraction angiography (DSA).Evidence of cerebral hypoperfusion on magnetic resonance imaging (MRI) arterial spin labelling (ASL) within the territory of the occluded ICA, defined as a ≥ 30% reduction compared with the contralateral hemisphere.Modified Rankin Scale (mRS) score of 0–3 at baseline.Preserved language comprehension, with no more than mild motor aphasia and no significant cognitive impairment.Adults aged 18–80 years.Provision of written informed consent by the patient or a legally authorised representative.Willingness and ability to comply with follow-up assessments.

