### Statistical analysis

Continuous variables will be reported as mean with standard deviation or median with interquartile range, depending on distribution. Categorical variables will be presented as frequencies and percentages. The primary outcome, change in cerebral hemodynamic status from baseline to 6 months, will be analyzed using a paired t-test or Wilcoxon signed-rank test, depending on data distribution. Mean change in CBF and/or perfusion asymmetry will be reported with 95% confidence intervals.

Early postoperative and 6-month changes in neurological and cognitive scores will be analyzed using paired tests. Categorical outcomes, including graft patency, recurrent TIA or stroke, complications, and mortality, will be reported as proportions with 95% confidence intervals.

Where appropriate, exploratory regression analyses will be performed to identify factors associated with hemodynamic improvement and clinical outcomes. Potential predictors may include age, sex, baseline perfusion deficit, vascular risk factors, duration of symptoms, and preoperative neurological status. Given the limited sample size, multivariable models will be restricted to a small number of clinically relevant covariates.

Because repeated measurements will be obtained from the same participants, analyses will account for within-subject correlation. Continuous repeated outcomes will be analysed using linear mixed-effects models, with time point entered as a fixed effect and participant ID as a random intercept. This approach allows estimation of postoperative change while accounting for correlation between repeated measures within individuals and accommodating incomplete follow-up data under a missing-at-random assumption.

A p-value <0.05 will be considered statistically significant. All analysis will be performed using Stata 19.5.

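### The haemodynamic outcome accepts an unnormalised rise in affected-side CBF on its own, so a whole-brain CBF shift would be classed as improvement

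*Protocol article*

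**What the plan says.** The Definitions of outcomes section lists the change in cerebral haemodynamic status from baseline to 6 months, measured by ASL MRI and "defined as a quantitative increase in regional CBF in the affected hemisphere and/or a reduction in interhemispheric perfusion asymmetry compared with baseline". It sets no minimum change, and no reference region for the CBF limb.

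The Statistical analysis section treats this change as primary: "The primary outcome, change in cerebral hemodynamic status from baseline to 6 months, will be analyzed using a paired t-test or Wilcoxon signed-rank test". It leaves the variable open in the same way: "Mean change in CBF and/or perfusion asymmetry will be reported with 95% confidence intervals". There is no control arm.

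Elsewhere the article does use a side-to-side measure. The inclusion criterion for hypoperfusion is "defined as a ≥ 30% reduction compared with the contralateral hemisphere", and Table 1 collects CBF asymmetry indices preoperatively, immediately after surgery and at 6 months.

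On equipment, the Radiological assessment text below Table 1 says: "MRI perfusion studies will be conducted before surgery on 1.5 or 3 Tesla MRI". The article does not say whether each patient stays at one field strength across visits.

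**The concern.** With the two limbs joined by and/or, a rise in affected-hemisphere CBF is sufficient by itself. A paired test against zero on absolute CBF cannot tell a rise on the grafted side from an equal rise across the whole brain. Any cause that moves the cohort's CBF between visits would produce such a rise, for example systemic conditions at the scan or a change between 1.5 T and 3 T. Without a control arm, normalisation within each scan is the available protection, and the definition does not require it.

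Two uses of the measure are at stake:

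- **The test itself.** The Statistical analysis section calls this outcome primary. The paired-means sample size also fits a continuous pre-post outcome of this kind, although the Primary objective, Primary endpoint and Definitions of outcomes sections name ischaemic stroke.
- **The link to recovery.** The Discussion plans to correlate perfusion change with neurological and cognitive change. CBF variation that does not come from the graft would enter that correlation as well.

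**Working it through.** **Inputs from the Sample size calculation section.** Two-sided α 0.05, 80% power, standardised effect 0.40, within-subject correlation ρ = 0.5, 52 evaluable patients, target 60, power 73% to 98% for ρ from 0.3 to 0.7.

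**Step 1: reproduce the plan's own figures.** For a paired t-test the effect on the change scale is d = 0.40 / √(2(1 − ρ)). At ρ = 0.5 this is 0.40 / 1 = 0.40. With the noncentral t distribution:

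- n = 52 gives power 80.8%, and n = 51 falls just short of 80%, so 52 is right.
- n = 60 gives 86.2%.
- At n = 60, ρ = 0.3 gives d = 0.338 and power 73.1%; ρ = 0.7 gives d = 0.516 and power 97.6%.

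The stated figures reproduce and are not in dispute.

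**Step 2: put in a shift with no bypass effect.** The documents give no SD for CBF and no size for any shift, so both are assumptions here. Let CV be the between-patient SD of regional CBF divided by its mean, and let g be a uniform shift as a fraction of the mean. Then SD of change / mean = CV × √(2(1 − 0.5)) = CV, so d = g / CV.

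Chance of a significant change in absolute affected-side CBF, two-sided 0.05, n = 52:

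| g | CV 20% | CV 25% | CV 30% |
|---|---|---|---|
| 5% | d = 0.25: 42% | d = 0.20: 29% | d = 0.167: 22% |
| 10% | d = 0.50: 94% | d = 0.40: 81% | d = 0.333: 65% |

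At n = 60 the rows become 48%, 33%, 25% and 97%, 86%, 72%.

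The table adds the same amount to every patient. If the shift is strictly proportional, the follow-up SD also grows, and SD of change / mean = CV × √(1 + (1 + g)² − 2 × 0.5 × (1 + g)). At n = 52 the ranges then become 41% to 21% for a 5% shift and 92% to 61% for a 10% shift. The picture is the same.

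**Step 3: compare the two limbs.** A simulation used 60 patients, CV 20%, mean CBF 50 on the contralateral side and 35 on the affected side (a 30% deficit), 5% hemisphere-specific noise, a proportional global shift and no bypass effect. These inputs are also assumptions. The chance of a significant result in the direction of improvement was:

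| Global shift | Rise in absolute CBF | Fall in asymmetry | Either limb |
|---|---|---|---|
| 0 | 2.7% | 2.4% | 4.9% |
| 5% | 41% | 2.5% | 42% |
| 10% | 93% | 2.3% | 93% |

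The nominal rate for one direction is 2.5%. The asymmetry limb stays there because a proportional shift cancels in the ratio. The problem comes entirely through the unnormalised limb.

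**The case against.** A reader might go further and infer that the scans are known to be taken under different systemic conditions. The documents do not say so. The Perioperative management section states that "Systolic blood pressure targets were maintained within a predefined range to ensure adequate bypass perfusion while minimizing the risk of hyperperfusion-related complications", but in the setting of intensive-care monitoring. It does not tie that range to the time of a scan. The early scan is a separate comparison: "At 3–5 days postoperatively, ASL-based MR perfusion imaging will be conducted to evaluate cerebral perfusion changes compared with preoperative studies". The definition at issue covers baseline to 6 months, and for that interval no difference in conditions is documented. This objection stands.

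Other parts of the case against also stand:

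- The percentages rest on an assumed CV and an assumed shift in one direction. Differences between patients that share no direction would add noise and cost power, but would not bias the mean.
- In the scenario above mean CBF really has changed; only attributing it to the graft would be wrong. The Limitations section already calls the findings associative and rules out definitive causal inference, so it would be too strong to say that the authors will report a shift as an effect of bypass.
- The absence of scan-time blood pressure or haematocrit from Table 1 is not a fault in a condensed article whose imaging parameters sit in S1 Table. Adjusting for such variables after surgery would in any case be debatable, because they are measured after the intervention.
- Asymmetry is collected at every scheduled visit, so reporting both limbs would expose a global shift.

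The last point does not answer the concern. The and/or wording does not require both limbs to be reported, and a rise in absolute CBF alone still satisfies the stated rule. The associative caveat limits causal language but does not change what is classed as improvement.

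**Conclusion.** The point holds as a flaw in a stated rule. The outcome definition and the analysis text both leave the haemodynamic measure open, and they let a change unrelated to the graft qualify as improvement. That follows from the wording and needs no assumption about scan conditions.

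The size is conditional. At n = 52 and ρ = 0.5, a 5% shift would be significant in about 42% to 22% of trials, and a 10% shift in about 94% to 65%, for CV from 20% to 30%. These figures show how sensitive the unnormalised limb is. They do not estimate this trial's error rate, because the documents give neither a CV nor evidence that any shift occurs. The planned sample size is unaffected.

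The change is worth making because it is cheap and because the entry criterion is already referenced to the contralateral side.

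**What to change.** In both the Definitions of outcomes and the Statistical analysis sections, replace and/or with one prespecified measure normalised within the scan and used at all three scheduled visits. Two candidates fit: the interhemispheric asymmetry index already in Table 1, or the ratio of operated-side CBF to CBF in a reference region. Report absolute CBF of both hemispheres as supportive, and state that an absolute rise is not called improvement when the reference side rises equally.

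The asymmetry index is already scheduled; a reference-region ratio is a recalculation from the existing maps if the region lies within ASL coverage. Neither needs new patients or scans.

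There are three drawbacks to state. A ratio adds some measurement noise. The contralateral side may itself change after bypass. Asymmetry remains open to regression to the mean, because entry requires a deficit of at least 30%, so a fall in asymmetry in one arm still needs cautious reading.

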### Data management

The collected data will be meticulously entered into a database, where revascularisation progress, the development of collateral circulation, and perfusion changes correlated with neurological and cognitive shifts will be evaluated. All data will undergo statistical processing and analysis to identify patterns and correlations, as well as survival analysis to assess collateral development and psychoneurological dynamics. All participants are expected to complete study visits over the planned 6-month follow-up period.

#### Sample size calculation.

Sample size estimation was performed in Stata (version 19.5) using the power pairedmeans command, based on a paired pre-post comparison of the primary outcome. Assuming a two-sided α of 0.05, 80% power, a standardised effect size of 0.40, and a within-subject correlation of 0.5, 52 evaluable patients were required. Allowing for potential loss to follow-up, a target sample size of 60 patients was set, providing approximately 86% power. Sensitivity analyses indicated that power ranged from 73% to 98% across plausible within-subject correlations (0.3–0.7).

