### Limitations

This study has several limitations. First, its single-center, open-label design may limit the generalizability of the findings and introduces a potential risk of selection bias. However, conducting the study in a high-volume tertiary neurosurgical center ensures consistency in surgical technique, perioperative management, and imaging protocols.

Second, the absence of a non-surgical control group precludes direct comparison between surgical revascularisation and best medical therapy. Nevertheless, the primary objective of this study is not to reassess the efficacy of STA-MCA bypass versus conservative treatment, but rather to investigate detailed hemodynamic, neurological, and cognitive changes following bypass surgery in a carefully selected population with documented cerebral hypoperfusion.

Third, the planned sample size of 60 participants was primarily determined based on feasibility considerations, including the recruitment capacity of our center, the predefined study duration, and the scope of the funded grant project. As a result, the planned sample size may limit statistical power for detecting small effect sizes and for building robust predictive models. Therefore, multivariable analyses will be considered exploratory, and results will be interpreted cautiously. Larger multicenter studies will be required to externally validate the findings.

Fourth, the single-arm study design without a control group limits the ability to control for confounding factors and precludes definitive causal inference regarding the observed effects. As a result, the findings should be interpreted as associative, and residual confounding cannot be excluded despite adjustment in exploratory analyses.

Fifth, cognitive assessment may be influenced by learning effects, mood, fatigue, or educational background. To mitigate these factors, standardized testing conditions will be applied, parallel test versions will be used when available, and cognitive reserve indicators will be incorporated into the analysis.

Sixth, advanced imaging techniques such as ASL MRI and intraoperative ICG FLOW800 analysis require specialized equipment and expertise, which may limit reproducibility in lower-resource settings. However, these techniques provide unique insights into cerebral hemodynamics and represent a major strength of the study.

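### The stated sample size and power come from a paired-means calculation that fits 6-month hemodynamic change, not the declared primary endpoint of ischemic stroke incidence

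*Protocol article*

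**What the plan says.** The protocol article names two different primary outcomes.

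- **Stroke incidence.** The Abstract (Methods), Primary objective, Primary endpoint and Definitions of outcomes sections all give 6-month ischemic stroke. The Primary endpoint reads "To evaluate the incidence of ischemic stroke during the 6-month follow-up period after surgery". Definitions of outcomes is explicit: "The primary outcome is defined as the incidence of ischemic stroke during the 6-month follow-up period after surgery". The last paragraph of the Introduction widens this to stroke or TIA.
- **Hemodynamic change.** The Statistical analysis section says "The primary outcome, change in cerebral hemodynamic status from baseline to 6 months, will be analyzed using a paired t-test or Wilcoxon signed-rank test". Definitions of outcomes lists the same quantity among the secondary outcomes: "changes in cerebral haemodynamic status from baseline to 6 months after surgery will be assessed using ASL MRI".

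The Sample size calculation section says the study was sized with Stata's paired-means power command, "based on a paired pre-post comparison of the primary outcome". Its inputs are "Assuming a two-sided α of 0.05, 80% power", a standardised effect of 0.40 and a pre-post correlation of 0.5. It reports 52 evaluable patients, a target of 60 to allow for loss with about 86% power, and 73% to 98% power for correlations from 0.3 to 0.7.

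In Statistical analysis, stroke appears only together with TIA, among categorical outcomes to be reported as proportions with 95% confidence intervals. The Limitations section adds that "the planned sample size of 60 participants was primarily determined based on feasibility considerations".

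**The concern.** A paired-means calculation needs a value before and after surgery in the same patient, a standard deviation, and a correlation between the two values. Stroke within six months of surgery has none of these: it is observed once, after surgery, as yes or no. No choice of inputs makes the method apply to it.

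A reader who takes the primary outcome from Definitions of outcomes and the power from Sample size calculation would credit the stroke endpoint with 80% to 86% power. The article gives no expected stroke rate, reference rate, hypothesis or target interval width. What the study can say about its declared primary endpoint is therefore set by the width of a confidence interval, and the article does not report that width.

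**Working it through.** **Step 1. Reproduce the stated figures.** Inputs, all from Sample size calculation: two-sided alpha 0.05, standardised effect d = 0.40, correlation rho = 0.5.

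- Effect on the paired difference: dz = d / sqrt(2(1 − rho)). At rho = 0.5 this is 0.40 / sqrt(1) = 0.40.
- Power = P(|T| > t(0.975, n − 1)), where T is noncentral t with n − 1 degrees of freedom and noncentrality dz × sqrt(n).

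| n | rho | dz | Power | Stated |
|---|---|---|---|---|
| 51 | 0.5 | 0.400 | 79.99% | – |
| 52 | 0.5 | 0.400 | 80.8% | 80% |
| 60 | 0.5 | 0.400 | 86.2% | about 86% |
| 60 | 0.3 | 0.338 | 73.1% | 73% |
| 60 | 0.7 | 0.516 | 97.6% | 98% |

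The smallest n reaching 80% is 52, as stated. Every figure reproduces for a continuous paired measure.

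A side point: the 86% and the 73% to 98% range take all 60 patients as evaluable, although 60 was chosen to allow for loss. At 52 evaluable, power is 80.8%, with a range of 66.7% to 95.5% for correlations from 0.3 to 0.7.

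**Step 2. Match the calculation to an outcome.**

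| Requirement of the method | 6-month stroke | 6-month hemodynamic change |
|---|---|---|
| Value before surgery | No | Yes (ASL MRI, Table 1) |
| Mean and SD of a paired difference | No | Yes |
| Pre-post correlation | No | Yes |
| Paired test planned | No; proportion with 95% CI | Yes; paired t-test or Wilcoxon |

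The calculation fits the outcome that Statistical analysis calls primary. It cannot fit the one that Definitions of outcomes calls primary.

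**Step 3. What the study size gives for stroke incidence.** No sample size for stroke can be derived from the article, because it states no rate and no target width. The event counts below are assumptions for illustration, and six-month stroke status is taken as known for everyone in the denominator. Exact (Clopper-Pearson) 95% limits for x events in n patients are:

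- lower = the 0.025 quantile of Beta(x, n − x + 1), or 0 when x = 0;
- upper = the 0.975 quantile of Beta(x + 1, n − x).

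For x = 0 the upper limit is 1 − 0.025^(1/n), which is 6.0% at n = 60 and 6.8% at n = 52.

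| Assumed strokes | n = 60 | n = 52 |
|---|---|---|
| 0 | 0% (0 to 6.0%) | 0% (0 to 6.8%) |
| 3 | 5.0% (1.0 to 13.9%) | 5.8% (1.2 to 15.9%) |
| 6 | 10.0% (3.8 to 20.5%) | 11.5% (4.4 to 23.4%) |

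With 3 strokes among 60 the interval spans 13.9 − 1.0 = 12.9 percentage points. With 6 it spans 20.5 − 3.8 = 16.7.

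**The case against.** The best defence is that Sample size calculation and Statistical analysis agree with each other. Both treat the primary outcome as a continuous pre-post change, and read together they form a coherent plan. On that view nothing is wrong with the calculation, and the fault lies in the sections that name stroke. This stands in part: the root defect is two competing primary outcomes, and rewriting the sample size section alone would leave Statistical analysis still calling hemodynamic change primary. It does not remove the mismatch, because four sections, including the formal definition, name stroke.

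A second defence is that a descriptive single-arm incidence needs no power. The Discussion says the study is not designed to compare bypass with conservative treatment, and an interval is already planned for recurrent TIA or stroke. This also stands. The fair criticism is that no precision for stroke was stated or justified, while a power figure is attached to the words primary outcome.

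A reader might also infer that the feasibility remark in Limitations contradicts the power calculation. The documents do not support that much. A size set primarily by feasibility can still be accompanied by a supporting calculation. The two accounts of 60 (feasibility, and 52 plus an allowance for loss) are in tension and need aligning, but they do not exclude each other.

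**Conclusion.** The point holds, as a mismatch between endpoint and sample size. The 52, the 86% and the 73% to 98% are correct for a continuous paired measure and do not belong to 6-month stroke incidence. This rests only on the article's own definitions. The interval widths for stroke rest on assumed event counts and show scale only; they do not measure an error.

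Two stronger readings should be resisted. One is that the sample size arithmetic is wrong; it reproduces in full. The other is that the primary outcome was changed at some stage. The Ethics section says outcome measures were predefined and remained unchanged after the retrospective registration, but nothing in the article shows which of the two was the predefined primary. Only the sponsor can settle that.

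The correction is essential because it concerns the stated basis for the primary endpoint.

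**What to change.** Reconcile Primary endpoint and Definitions of outcomes with Sample size calculation and Statistical analysis, and state openly which outcome was the predefined primary. If the sponsor's records show it was hemodynamic change, the sections naming stroke must be corrected and that said plainly. If it is stroke incidence, as four sections say:

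1. In Statistical analysis, stop calling hemodynamic change the primary outcome. Name stroke incidence with an exact 95% confidence interval as the primary analysis; Mortality analysis already specifies exact intervals for deaths.
2. In Sample size calculation, attach the paired-means calculation to one named ASL measure as a secondary outcome, and remove any power claim for the primary.
3. Give the expected exact intervals for stroke incidence at event counts labelled as assumptions, such as those tabulated above for 60 and 52 patients, and state that no hypothesis is tested.
4. Align the account of the 60 patients with Limitations, which says the number was set primarily by feasibility.

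The cost is text only. The sample size justification becomes less favourable, and no extra patients are needed.
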